#### Inclusion criteria

3.1.1

Patients will be included if they satisfy the following criteria:

(1)comply with the diagnostic criteria for psoriasis vulgaris as indicated in dermatovenerology 8th Edition;(2)comply with the diagnostic criteria for blood-heat syndrome as indicated in the Guidelines for the Clinical Research of Chinese Medicine New Drugs and New Dermatology of Traditional Chinese Medicine;(3)must be aged between 18 and 70 years;(4)An informed consent is provided; and(5)recurrent psoriasis patients must belong to the types of recurrence IV, V and VI^[12,13]^: Type IV (frequently limited type): The rash is extensive or limited at the first onset, and rashes occur every year afterward, but the amount of rash is small and is limited to certain parts of the body; Type V (frequently sparsely sparse): Psoriasis often recurs, with a wide range of rashes at the onset, but with a sparse density; Type VI (frequently issued): Psoriasis occurs every year, and the rash is widely distributed and numerous.

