#### Primary outcomes

3.5.1

(1)PASI: assess the severity of the disease.(2)Laboratory assessments: the number and distribution of Th1, Th2, Th17, Treg, Th22, and Th9 cells will be determined by ELISA. The expression of the transcription factors T-bet, GATA3, ROR gamma t, Foxp3 gene will be investigated by PCR and WB. The screening of cytokines, such as IFN-gamma, IL-4, IL-17A, IL-17F, IL-22, TGF-beta, IL-10 and IL-9 will be performed by Bio-Plex suspension chip.(3)Recurrence rate = recurrence cases/follow-up cases ∗100%

Note:

No recurrence criteria: the same as the end of treatment and lesion limitation. Recurrence criteria: new skin lesions appearing in the patients who were clinically cured or have the original skin lesions expanding, the color turning red, the scale increasing and the PASI score increasing for ≥ 1.

(1) Mitigation period: this remission period - the last remission period.

Note:

The last remission period: the time from the last clinical cure to the recurrence. This remission: the time interval from the end of JWLXXF treatment to the next recurrence.

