### Clinical efficacy evaluation basis

4.2

For moderate and severe psoriasis, PASI score is still the “gold standard” to evaluate the severity of psoriasis.^[29]^ According to the research, patients with sustained and efficient response to PASI score have a better quality of life score.^[30]^ According to the requirements of the new drug effective standard, after three months of test, the effective standard is a 75% improvement of the PASI score, which is called PASI75.^[29]^ PASI75 combined, with the pruritus score and DQOLS, can evaluate the short-term efficacy of JWLXXF. It needs a certain time to follow up on the recurrence rate and remission period to determine the long-term effect. After 8 weeks of treatment, patients with a pai75 will be followed up and this period will start from the end of the treatment. If there is no recurrence, the follow-up period is 1 year. If there is recurrence, the recurrence of the disease is the end point of the follow-up.

According to the guiding principles for clinical research on new drugs of traditional Chinese medicine (Part III), issued by the Ministry of health in 1997 and the directions of new drugs clinical research (try out) issued by the State Food and Drug Administration in 2002, the recurrence criteria are: new skin lesions appear in the patients who are cured clinically, or the original skin lesions expand, turn red, scale increase, and PASI score increase for ≥1. No recurrence criteria: the same as that at the end of treatment, but with limited skin lesions.^[31]^

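### The 1-point PASI rise that defines recurrence is not scaled to baseline severity, yet recurrence among week-8 responders is compared with an unadjusted chi-square test

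*Protocol article*

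**What the plan says.** Section 3.5.1 (Primary outcomes) lists the recurrence rate, recurrent cases over followed-up cases, as a primary outcome. Recurrence means "new skin lesions appearing in the patients who were clinically cured or have the original skin lesions expanding", with reddening, and with "the scale increasing and the PASI score increasing for ≥ 1". Section 4.2 (Clinical efficacy evaluation basis) repeats the rule, giving the second route as "or the original skin lesions expand, turn red, scale increase, and PASI score increase for ≥1", and attributes it to two national guidance documents. There are thus two routes to recurrence, and only one number: a PASI rise of at least 1 point. Non-recurrence is described by reference to the state at the end of treatment, so I read the rise as measured from week 8.

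Entry to follow-up is relative. The Abstract and section 2 (Methods/design) admit patients whose PASI improved by more than 75% at week 8.

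Section 3.1.1 (Inclusion criteria) admits three recurrence types. At one end is type IV, where rashes recur "but the amount of rash is small and is limited to certain parts of the body". At the other is type VI: "Psoriasis occurs every year, and the rash is widely distributed and numerous". The section states no minimum PASI.

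Section 3.10 (Statistical analysis) names the chi-square test for comparing the two groups on the primary outcomes. Section 4.2 makes recurrence the end point of follow-up.

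**The concern.** A patient enters follow-up by a rule proportional to baseline PASI and leaves it as recurrent by a rule fixed in points. Over a wide severity range the same label then describes different events. In mild disease a 1-point rise is the loss of most of the benefit; in extensive disease it is a small part of it.

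This matters because recurrence is a primary outcome and the trial's stated objective, and because it is assessed only in responders, a subset formed after randomisation from 36 patients per arm. The severity mix of that subset can differ between arms by chance, or because the two treatments produce a 75% response in different kinds of patient. If the chance of being counted as recurrent rises with baseline PASI, a difference in mix can show up as a difference in recurrence rate, and a plain two-by-two comparison cannot separate the two.

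**Working it through.** The plan gives no figure on this point to reproduce. The check is direct arithmetic on the definition.

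**Inputs**
- Recurrence threshold on PASI: a rise of at least 1 point (sections 3.5.1 and 4.2).
- Entry to follow-up: improvement above 75% (Abstract, section 2), so week-8 PASI is below 0.25 × B, where B is baseline PASI. Exactly 75% is the limiting case.
- Distribution of B: not given. The values below are assumed, to show the range.

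**Step 1: share of the gain that 1 point represents.** The gain at week 8 is 0.75 × B at exactly 75% improvement and B if the skin has cleared. One point is therefore 1/(0.75 × B) of the gain in the first case and 1/B in the second.

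| Baseline PASI (assumed) | Week-8 PASI at 75% | Gain at 75% | 1 point as share of gain, at 75% | 1 point as share of gain, if cleared |
|---|---|---|---|---|
| 1 | 0.25 | 0.75 | 133% | 100% |
| 1.33 | 0.33 | 1.0 | 100% | 75% |
| 2 | 0.5 | 1.5 | 67% | 50% |
| 5 | 1.25 | 3.75 | 27% | 20% |
| 10 | 2.5 | 7.5 | 13% | 10% |
| 20 | 5 | 15 | 6.7% | 5% |
| 30 | 7.5 | 22.5 | 4.4% | 3.3% |

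Between baselines 2 and 20 the share falls tenfold, from two thirds of the gain to one fifteenth.

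**Step 2: high baseline.** A patient who goes from 20 to 5 and then to 6 satisfies the PASI component while still (20 − 6)/20 = 70% improved on baseline.

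**Step 3: low baseline.** A full return to baseline is a rise of 0.75 × B to B. It is below 1 when B < 1/0.75 = 1.33 for a patient at exactly 75% improvement, and when B < 1.0 for a cleared patient. For example, 1.0 falling to 0.2 is an 80% improvement, and a complete return is a rise of 0.8, short of the threshold.

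**Step 4: what the other parts of the definition change.** The original-lesions route also requires expansion, redness and more scale, so at high baseline PASI noise alone is not enough. No size is attached to those signs, so the 1-point rise remains the only stated amount of change. At low baseline, the new-lesions route can count a relapse that the PASI component misses, but it is confined to clinically cured patients, while follow-up admits anyone above 75% improvement, including patients with residual lesions.

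**The case against.** The strongest case on the other side has four parts.

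- **The rule is sourced and may be aimed at onset.** The definition comes from national guidance. A rise of 1 point with lesions expanding, reddening and scaling is plausibly the start of a relapse, which is what a remission period should time. This stands: it is a reason to keep the definition as the main one, and not to call a recurrence at 6 after 20 to 5 a trivial change.
- **A relative rule depends on baseline too.** A 50% loss is 0.4 points for the patient going from 1.0 to 0.2, and 7.5 points for the patient going from 20 to 5. Nothing in the article supports 50% in particular. This also stands, and it is why the relative rule belongs in a sensitivity analysis.
- **Chance imbalance is already covered by the test's error rate, and a condensed article may leave covariates to a fuller document.** In part. Missing detail on stratification or covariates is no fault here. But the article does name the chi-square test for the primary outcomes. The comparison is also confined to responders, so differences in severity mix need not be due to chance alone.
- **The effect on the between-arm result is not quantified.** Correct. The table shows what the threshold means for a single patient, not a bias in the trial result.

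A reader might infer that recurrence is nothing more than a 1-point PASI rise, or that full relapses will be missed in this trial. The documents support neither. There is a separate new-lesions route and a joint requirement for clinical signs. A missed full relapse is possible only below a baseline of about 1.0 to 1.33. Type IV is described as small and limited, but nothing equates it with PASI that low.

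**Conclusion.** The point holds in a limited form. The only numeric recurrence threshold is absolute, and it is applied after a relative entry rule to a population with no PASI floor. At 75% improvement it stands for 67% of the gain at baseline 2, 13% at 10 and 6.7% at 20. At very low baseline PASI it could be out of reach even on full relapse.

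That the chance of being counted as recurrent depends on baseline severity rests on one assumption: relapse tends to proceed in proportion to the improvement gained, so a small fractional loss is reached sooner or more often than a large one. How far this could move the between-arm comparison cannot be worked out, because neither the baseline PASI distribution nor the number of responders per arm is given. The analysis should change; the main definition of recurrence need not.

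**What to change.** 1. Keep the guideline definition as the main recurrence outcome.
2. In section 3.10, replace the unadjusted chi-square for recurrence with a between-arm comparison from a model adjusted for baseline PASI. Add recurrence type (IV, V, VI) only if the number of responders allows.
3. Prespecify a sensitivity outcome: loss of at least 50% of the PASI improvement from baseline to week 8.
4. So that this outcome can be observed, keep the PASI assessments already scheduled after a first recurrence, for data collection only. Record any new psoriasis treatment, and state beforehand how PASI after such treatment will be handled.

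Baseline, week-8 and follow-up PASI are already collected, so items 2 and 3 need only wording. Item 4 has a cost: some patients attend scheduled visits they would otherwise not have had, and later PASI may reflect new treatment. Section 4.4 (Trial status) reports 60 patients already recruited, so anyone whose follow-up has already ended at recurrence will lack the later scores. Adjustment must be parsimonious because responders are few. It reduces the effect of a different baseline PASI mix but does not restore the randomised comparison lost by restricting to responders.

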**Figure 1 F1:**
[figure not shown]
Test flow chart.

Potential participants will be invited to an initial assessment (first visit) consisting of an inclusion and exclusion criteria screening. If eligible, participants will be asked for informed consent and will undergo assessment of Psoriasis area severity index (PASI), dermatology life quality index (DQOLS), and score of Pruritus Degree by PGA, lesion photos and vital signs, full blood count, kidney and liver function blood tests, electrocardiogram, stool examination and urine (routine chemical examinations).

A total of 72 patients with recurrent PV will be randomized (in a 1:1 ratio) to receive oral Chinese herbal medicine JWLXXF or oral acitretin for 8 weeks. During the observation phase, psoriasis symptom measures will be self-reported by participants and recorded in a daily or weekly diary. Face-to-face assessments with blinded assessors will be scheduled at weeks 2, 4, 6, and 8 (Fifth visit), with further data collected, including assessment of PASI, DQOLS, and score of Pruritus degree by PGA, lesion photos, drug adherence, vital signs, adverse events and cause analysis of shedding (Table 1). The conversation will be made to 72 patients, at the time of medical treatment, to check adherence to the dosage guidelines and to monitor adverse events. Routine chemical examinations, laboratory assessments of efficacy and safety evaluation will also be scheduled at the end of the 8-week period.

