### Randomization

3.4

Unpredictable randomized sequences were generated by computer and sealed in opaque and sequentially encoded envelopes. After determining the eligibility of the participants, the researchers will break the envelopes in order and assigned them to the appropriate test group. The person who will generate the random sequence will not be the same person as the assigned subject, and the random assignment will not be displayed until the end of the study.

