### Statistical analysis

3.10

SPSS Statistics 17.0 (IBM SPSS Inc., Armonk, NY) will be used for the statistical analysis of data, which will be carried out by independent statisticians. The Chi-square test will be used to evaluate the basic baseline characteristics and primary outcomes of the 2 groups. The Spearman rank correlation analysis of the correlation between PASI and biochemical indexes, will be used. The secondary outcomes will be evaluated by means, standard deviations and medians. The one way ANOVA test will be used to compare the mean of multiple samples, the LSD test for the homogeneous variance, and the Tamhane T2 test for the uneven variance. *P* < .05 will be considered as statistically significant.

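### A primary outcome subtracts the last remission one for one: this is never more precise than linear covariate adjustment, and it has no observed value for patients relapse-free at 1 year

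*Protocol article*

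**What the plan says.** Section 3.5.1 (Primary outcomes) of the protocol article gives "Mitigation period: this remission period - the last remission period" and defines the two terms: "The last remission period: the time from the last clinical cure to the recurrence" and "This remission: the time interval from the end of JWLXXF treatment to the next recurrence". The same difference appears in section 2 among the data collected in follow-up.

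Section 3.10 (Statistical analysis) states "The Chi-square test will be used to evaluate the basic baseline characteristics and primary outcomes of the 2 groups" and, for means, "The one way ANOVA test will be used to compare the mean of multiple samples". It names no covariate. Section 3.4 says "Unpredictable randomized sequences were generated by computer and sealed in opaque and sequentially encoded envelopes" and gives no stratification factor.

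Follow-up is limited to patients whose PASI improved by more than 75% (section 2). It ends at recurrence, or at 1 year if there is none (section 4.2). The article gives no SD for either remission period and no correlation between them.

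**The concern.** The last remission belongs to the patient's history before entry. Subtracting it is a form of baseline adjustment, but with the coefficient fixed at 1 instead of estimated. If the two remissions are only loosely related, the subtraction carries the spread of the earlier interval into the outcome and removes little in return. The comparison can then be less precise than one that ignores the last remission altogether.

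The difference also needs an end date for this remission. A patient who has not relapsed when follow-up stops has none, and these are the patients in whom a treatment meant to prevent relapse has done best.

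Both points rest on a rule that the article states, not on detail it leaves out. The number of patients who will reach follow-up is not given but cannot exceed 36 per arm, so precision matters.

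**Working it through.** **Inputs.** From the article: the outcome is this remission (Y) minus last remission (X); X precedes randomization; Y is followed for at most 52 weeks (weeks 9 to 60). Assumed, because the article is silent: the correlation r of X and Y, from 0 to 0.7, and k = SD(X)/SD(Y), from 0.5 to 1.5. This remission is taken to start at the end of allocated treatment in both arms, although the definition names JWLXXF only.

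**Step 1: variances, in units of Var(Y).**
- Ignoring X: 1
- Subtracting X: Var(Y − X) = 1 + k² − 2rk
- Linear adjustment for X: 1 − r²

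**Step 2: subtraction against adjustment.** (1 + k² − 2rk) − (1 − r²) = (k − r)². This is never negative. It is zero only when r = k, where the regression slope r/k happens to equal 1.

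**Step 3: subtraction against ignoring X.** 1 + k² − 2rk exceeds 1 when r < k/2. The break-even correlation is 0.25 for k = 0.5, 0.375 for k = 0.75, 0.50 for k = 1 and 0.75 for k = 1.5.

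**Step 4: figures.**

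| r | Adjustment (any k) | Subtraction, k = 0.5 | k = 0.75 | k = 1 | k = 1.5 |
|---|---|---|---|---|---|
| 0 | 1.00 | 1.25 | 1.56 | 2.00 | 3.25 |
| 0.3 | 0.91 | 0.95 | 1.11 | 1.40 | 2.35 |
| 0.5 | 0.75 | 0.75 | 0.81 | 1.00 | 1.75 |
| 0.7 | 0.51 | 0.55 | 0.51 | 0.60 | 1.15 |

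At r = 0.3 the penalty of subtraction over adjustment is 0.95/0.91 = 1.04 for k = 0.5, 1.40/0.91 = 1.54 for k = 1 and 2.35/0.91 = 2.58 for k = 1.5.

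**Step 5: the plan's sample size.** Section 3.8 states 30 per arm for 0.9 SD, 90% power and a 5% level. With a two-sided test, the normal formula gives 2(1.960 + 1.282)²/0.9² = 25.9, so 26; the t test gives 27. The stated 30 is therefore not reproduced but errs on the safe side, with about 93% power. It is not tied to the remission outcome and says nothing for or against this point. As an illustration only, with k = 1, r = 0.3 and a difference of 0.9 SD of the raw time, 90% power needs 27 per arm ignoring X, 38 with subtraction and 25 with adjustment.

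**Step 6: patients without relapse.** With no recurrence by 52 weeks, Y is known only to exceed 52, so Y − X is known only to exceed 52 − X. The formulas above assume that both intervals are observed and do not cover these patients.

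**The case against.** The strongest reply is that covariate choice is commonly left to a statistical analysis plan, which is not shown, and that an unadjusted comparison of randomized arms is valid. Both statements are right. The absence of a covariate is therefore not the point. What stands is the outcome definition itself: an analysis plan can add a covariate, but the stated outcome remains a one-for-one difference.

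A second reply is that the size of the loss is unknown. That is also right. A reader might infer that subtraction adds noise whenever the correlation is below 0.5, or that it costs 54% more patients than adjustment. Both figures need equal SDs, and the 54% needs r = 0.3 as well. The article supports neither assumption, and the 52-week limit on only one of the intervals makes equal SDs harder to presume. At k = 0.5 and r = 0.3 subtraction costs about 4% against adjustment and is slightly better than ignoring the last remission.

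A reader might also infer that recurrence type is a known predictor of relapse that has been wasted. Section 3.1.1 requires that "recurrent psoriasis patients must belong to the types of recurrence IV, V and VI", but it describes all three types as frequently recurring and separates them mainly by the extent and density of the rash. A link to relapse within this population is not shown.

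Finally, a reader might infer that many patients can only score as worse because their last remission exceeded 52 weeks. Types IV and VI recur yearly by definition and type V often, so such patients should be uncommon. The missing value for relapse-free patients does not depend on them.

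**Conclusion.** The point holds as a matter of efficiency and of outcome definition. For a continuous, fully observed outcome with a common linear slope, subtraction is never more precise than adjustment, one degree of freedom aside, whatever r and k are. Only the size depends on assumptions: at r = 0.3 the variance ratio runs from 1.04 to 2.58 as k goes from 0.5 to 1.5. These ratios do not carry over to a time-to-event model, and the gain from such a model cannot be computed from the article.

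The undefined difference for patients relapse-free at 1 year follows from sections 3.5.1 and 4.2 without any assumption.

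Two stronger readings are not supported. The last remission is not left unused, because subtraction is itself a crude adjustment. Nor does subtraction introduce bias: with arms comparable by randomization, the difference estimates the same contrast as the raw time. That protection is weaker among PASI responders, but this comes from selecting on response after randomization and affects every analysis of the subset.

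**What to change.** In sections 3.5.1 and 3.10, compare the arms on time from end of treatment to recurrence, censored at the end of follow-up, in a model with arm and last remission length as a covariate. Keep this remission minus last remission as a descriptive within-patient summary. Recurrence type may be added as a further covariate if the number of recurrences allows; it is optional.

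No new data are needed, since the subtraction already requires the last remission. The cost is one extra parameter and an effect that is conditional on last remission rather than marginal, which the report should state. The change should be fixed before the data are analysed. It does not repair the selection of patients into follow-up.

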**Table 1 T1:**
[figure not shown]
Evaluation measures and time points.

The 72 patients with recurrent PV, whose PASI scores improvement are more than 75%, will undergo a 52-week follow-up phase (week 9 to week 60), with further data collection, including assessment of PASI, routine chemical examinations, recurrence rate, remission period (This remission period - the last remission period) (Table 1).

For the 52-week follow-up phase, participants will continue to record symptoms in their daily or weekly diaries. At week 60, participants will attend an end of follow-up assessment (9th visit) which will mark the end of the trial.

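### The remission-period outcome listed as primary cannot be computed for patients still in remission at 52 weeks, names one arm only, and subtracts intervals with different starting points

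*Protocol article*

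**What the plan says.** Section 3.5.1 (Primary outcomes) includes "1) Mitigation period: this remission period - the last remission period". Its note defines the two terms:

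- Current term: "This remission: the time interval from the end of JWLXXF treatment to the next recurrence".
- Historical term: "The last remission period: the time from the last clinical cure to the recurrence".

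The text after Table 1 repeats the same difference as a follow-up measure, "remission period (This remission period - the last remission period", for the recurrent-psoriasis patients "whose PASI scores improvement are more than 75%, will undergo a 52-week follow-up phase (week 9 to week 60". Those patients were randomised "to receive oral Chinese herbal medicine JWLXXF or oral acitretin for 8 weeks", so both arms are meant to contribute.

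Section 4.2 starts follow-up at the end of treatment without naming an arm and ends it at recurrence. For the others it says: "If there is no recurrence, the follow-up period is 1 year".

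Section 3.10 says "The Chi-square test will be used to evaluate the basic baseline characteristics and primary outcomes of the 2 groups". It also names one-way ANOVA with LSD or Tamhane T2 comparisons for means, and Spearman correlation for PASI against laboratory measures. No survival method is named.

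**The concern.** The outcome is fixed as an arithmetic difference, and three features of its definition do not work.

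1. The start of the current remission is written for JWLXXF patients only.
2. The current remission ends only at a recurrence. A responder who completes the 52 weeks without one has no end date and therefore no difference. These are the patients with the best result.
3. The two intervals being subtracted begin at different states, and only the current one has a limit on how long it can be observed.

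The second feature matters most. If the treatments differ in relapse, the better arm has more patients without a value. An analysis of computable values alone would then compare relapsers with relapsers and miss most of the benefit the outcome was meant to show.

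**Working it through.** The plan gives no expected relapse rate or remission length, so it has no figure of its own to reproduce here. The definitions can be compared directly. The size of the effect needs assumed rates.

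**Comparison of the two terms**

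| | Last remission | This remission |
|---|---|---|
| Starts at | last clinical cure | end of JWLXXF treatment (3.5.1); end of treatment, no arm named (4.2) |
| Patient state at start | cured | PASI improvement above 75%, not stated to be cure |
| Ends at | recurrence | next recurrence |
| Longest observable value | no limit stated | 52 weeks |
| Value if no recurrence is seen | not applicable | none given |

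One consequence follows from the table alone. The largest difference a patient can show is 52 weeks minus the previous remission. A patient whose previous remission exceeded 52 weeks could not show a gain within follow-up, even without a relapse. Recurrence types IV and VI in section 3.1.1 are described as yearly, so this may be uncommon. For type V no yearly frequency is stated.

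**Effect of leaving out patients without a value (illustration)**

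Assumptions, not from the documents: exponential relapse times from the end of treatment, complete 52-week follow-up, and the 52-week recurrence proportions shown. Only the current-remission term is modelled.

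Let R be the 52-week recurrence proportion, S = 1 − R, and r = −ln(S)/52 per week.

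- Mean remission restricted to 52 weeks, all followed patients: R/r.
- Mean among relapsers only: 1/r − 52·S/R.

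Worked case, R = 70% versus 40%:

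- r = −ln(0.3)/52 = 0.02315 and −ln(0.6)/52 = 0.00982.
- Restricted means: 0.7/0.02315 = 30.2 and 0.4/0.00982 = 40.7 weeks; difference 10.5.
- Relapsers only: 43.2 − 52·0.3/0.7 = 20.9 and 101.8 − 52·0.6/0.4 = 23.8 weeks; difference 2.9.
- Followed patients without a value: 30% and 60%.

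The same formulas over a range (differences taken before rounding):

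| 52-week recurrence | Restricted means (weeks) | Difference | Relapsers only (weeks) | Difference |
|---|---|---|---|---|
| 60% v 30% | 34.1 v 43.7 | 9.7 | 22.1 v 24.5 | 2.4 |
| 70% v 40% | 30.2 v 40.7 | 10.5 | 20.9 v 23.8 | 2.9 |
| 90% v 60% | 20.3 v 34.1 | 13.7 | 16.8 v 22.1 | 5.3 |

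The share of the observable difference lost is 1 − 2.4/9.7 = 75%, 1 − 2.9/10.5 = 72% and 1 − 5.3/13.7 = 61%.

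**Methods named.** A chi-square test compares proportions, not a difference of durations. ANOVA needs a complete value for each patient. Neither takes a remission known only to exceed 52 weeks.

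**The case against.** The strongest reply is that most of this is recoverable or belongs in an analysis plan that is not shown. Section 4.2 already fixes when observation ends, which supplies an event time and a natural censoring time. How event-free patients are handled is commonly left to an analysis plan. The trial also calls itself a pilot. Part of this stands: the plan does not say that non-relapsers will be dropped, so the attenuation above is conditional. But the article does not merely omit a detail. It fixes a formula that cannot be evaluated without a recurrence date and names methods for primary outcomes that cannot use a censored time. An analysis plan could add a censoring rule, but it would still have to replace this definition.

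Four stronger readings are tempting and are not supported:

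- **That the acitretin arm has no usable outcome.** Taken alone, the section 3.5.1 wording suggests this. The text after Table 1 collects the measure in both arms and section 4.2 starts the clock neutrally, so it is probably a drafting slip. It still needs correcting, because section 3.5.1 is the formal definition.
- **That nearly all of the trial's relapse evidence would be lost.** Recurrence rate is a separate primary outcome with all followed cases in its denominator, so non-relapsers count there.
- **That the loss should be measured against uncapped means.** In the 70% versus 40% case these are 43.2 and 101.8 weeks, but they extrapolate past anything the trial can observe. The restricted means are the fair comparison.
- **That the historical term brings in recall error or biases the arms differently.** The article does not say how past remission is ascertained. The term precedes treatment and is defined identically for both arms, so the mismatch mainly adds noise and clouds the within-patient reading.

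**Conclusion.** The point holds as a defect in how one listed primary outcome is specified. As written, the remission difference has no value for any patient without recurrence within the 52-week follow-up, the named methods do not handle censoring, the current term is worded for one arm, and the two subtracted intervals do not start at comparable states.

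If non-relapsers were left out, roughly 60% to 75% of the difference observable within 52 weeks would disappear across the scenarios shown. That size rests on exponential relapse, complete follow-up and assumed recurrence proportions. The direction comes from excluding the longest remissions, which are more frequent in the better arm. The conclusion does not extend to the recurrence-rate outcome.

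**What to change.** In section 3.5.1, replace the difference with time from end of study treatment to first recurrence, in the same words for both arms, censored at week 60 or last contact if no recurrence is seen. In section 3.10, state that the arms will be compared among the patients in follow-up by Kaplan-Meier curves with a log-rank test or a Cox model. Enter previous remission length as a baseline covariate instead of subtracting it, and state how its starting point is defined.

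The cost is small: revised wording and a standard survival analysis. The existing formula already requires the previous remission length, and the planned follow-up already ends at recurrence or at one year, so no new assessments are needed. What is given up is the within-patient difference as the main measure. It can still be reported descriptively for patients who relapse, with the number lacking a value shown by arm. The change should be made before outcomes by arm are seen.
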